#### Recruitment

Participants are recruited from the VACHS by mailing letters to those who are identified via EHR review as having a back-pain-related diagnosis including low back and spine conditions and nerve compression (ICD-9 codes 724.02, 724.03, 724.2, 724.3, and 724.4) and a pain intensity rating of ≥ 4 (indicating moderate pain) [17] on the 0–10 NRS during their most recent clinic visit. Potential participants are called to solicit enrollment unless an “opt out” response is received by study staff, either by returning a pre-stamped and addressed letter or by telephone call. Additional participants are obtained through provider referral and advertisements placed in clinical care areas throughout the medical center and outpatient clinic locations of VACHS. Potential participants who respond to the referral or advertisement are screened by the study research assistant regarding key eligibility criteria for the study (e.g., confirmation of presence of chronic back pain of at least moderate intensity and absence of medical and psychiatric comorbidities that preclude eligibility). If initial screening suggests potential eligibility, a face-to-face appointment is scheduled for obtaining written informed consent and a full eligibility screening.

#### Baseline appointment

After consent, the final assessment of study eligibility is determined through review of the EHR by the study psychiatric advance practice registered nurse and psychologists, and participant responses to validated measures. The study nurse verifies the diagnosis of CLBP and uses a structured chart abstraction and assessment tool based on a classification system recommended in clinical practice guidelines [18] to identify the diagnosis and treatments of CLBP and classify participants’ pain as either non-specific low back pain, low back pain with a radicular component, or pain associated with other specific spinal causes. A trained research assistant under supervision of a psychologist reviews each participant’s chart to identify disqualifying psychiatric diagnoses or active suicidality. The research assistant administers a brief semi-structured interview to collect demographic and pain-related information, the Mini-International Neuropsychiatric Interview for DSM-IV (MINI) [19] to identify the presence of any DSM-IV psychiatric disorders, the Beck Depression Inventory-II (BDI-II) [20] to screen for severe depressive symptoms, and the SLUMS examination to screen for cognitive deficits likely to interfere with treatment participation. Prescribed pain medications and their dosage, as noted in the EHR, are recorded. Individuals who meet eligibility criteria are enrolled in the IVR system and TrialDB, a secure, encrypted clinical trials management database that facilitates participant randomization and collection and management of questionnaire data.

#### Randomization

Eligible participants are randomized to either in-person CBT or IVR-CBT immediately after completing the baseline assessments. The study research assistant enters the participant’s demographic information and stratification factors into TrialDB, which holds the randomization schedule and is masked from users thereby enabling concealed allocation. The treatment allocation ratio is 1:1 using a permuted stratified block design with variable block size. Randomization is done within strata defined by patients’ distance from the VACHS-West Haven campus (<10, 11–25, 26 or greater miles) and cause of low back pain as determined by the study nurse based on EHR review (non-specific low back pain, low back pain with a radicular component, or pain associated with other specific spinal causes) [18]. The research assistant informs a study therapist of the participant’s treatment assignment.

#### Pedometer, TrialDB, and IVR system training

The research assistant enrolls participants in the IVR system and TrialDB, a separate, secure, encrypted web-interface used for completing the study outcome measures. Participants are provided with training in the use of TrialDB, the IVR system and the study pedometer by a brief demonstration supplemented by written instructions included in the patient handbook. Participants’ stride length is measured and they are provided with an Omron Go Smart Model HJ-112 pocket pedometer to use in the walking portion of the CBT and IVR-CBT interventions.

#### Patient handbooks

At the end of the baseline appointment participants are given either a CBT or IVR-CBT patient handbook.The patient handbooks were adapted from materials used in a prior trial of in-person CBT for CLBP by psychologists with experience in the delivery of CBT for chronic pain [21]. The materials are written at a 6^th^ grade reading level and pictures and simple figures are incorporated as often as possible to enhance patients’ understanding and engagement. As a check on comprehension, participants are asked five true/false questions about each treatment module in the week it is presented. The IVR-CBT patient handbook and IVR scripts were pilot tested with 17 individuals with chronic pain who reviewed the materials and an additional four individuals who received treatment using the new materials. Both groups provided feedback via semi-structured interviews and revisions were made to the materials based on feedback.

#### Daily IVR calls

After enrollment, but prior to beginning treatment, participants receive seven daily IVR calls to assess their baseline pain intensity, pedometer-measured step counts and self-reported sleep duration in hours [22]. Starting on the first day of treatment and continuing for 70 days, participants receive daily IVR calls to answer seven daily questions that assess pain intensity, sleep quality and duration, pedometer-measured step count, catastrophizing (I worried my pain would never end”, “I felt my pain was so bad I could not stand it anymore”) and adherence to the current week’s skill practice goal. Once per week participants are asked to report: 1) any adverse events associated with the graduated walking portion of the treatment, 2) any increase or decrease in pain medication dose made on the advice of their physician or their own initiative, 3) how often they practiced their weekly, self-selected pleasant or meaningful activity goal and if it improved their happiness or satisfaction 4) if they continued to use any of the pain coping skills learned in prior weeks, and 5) their comprehension of the module material via five true/false questions about the week’s pain coping skill. All of the information reported during a call is automatically captured in a database and time and date stamped for later review by a therapist. Participants receive a call at their chosen time; if they do not complete the call, they are called again fifteen minutes after the designated time, and if they do not complete the second call, they are called again one hour later. If they do not answer any of these calls, the call day is considered missed and they are not called again until the following day. Participants have the option of calling into the system to make their daily report in circumstances when they are unavailable at the scheduled call time. The IVR system flags any instances of a participant missing the first call day or two consecutive call days, and the study research assistants contact the participant to assist them if there is a technical difficulty or to encourage adherence to the call schedule. When participants are unable to complete calls for an extended period of time such as during vacation, calls can be paused and resume when a participant returns. Participants are not paid for completing daily IVR calls.

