#### Outcomes

Survey outcomes are assessed at 4 time points, baseline, post-treatment, and 6 and 9 months post baseline. Participants are given up to 14 weeks to complete treatment in order to accommodate rescheduled sessions due to vacations, illness or travel difficulties. Post-treatment data are collected when a participant completes treatment or at 15 weeks post-baseline regardless of whether the participant has completed treatment. Survey outcomes are assessed using the TrialDB system, which allows participants to complete the self-report questionnaires online via a secure web-based interface. Participants who do not have an Internet connection may come to the medical center to complete the measures via TrialDB or complete a paper version of the measures and return them by mail. IVR outcomes will be assessed daily during the baseline week and over the 10 treatment weeks.

Measures were selected based on the Initiative on Methods, Measurement and Pain Assessment in Clinical Trials (IMMPACT) recommendations [23], which called for the assessment of multiple domains of the pain experience in all pain treatment trials and recommended measures based on their psychometric properties and respondent burden. These measures are consistent with CONSORT guidelines for non-inferiority trials [24] that recommend that outcome measures be similar to those used in studies to establish efficacy of the reference treatment.

*Primary Outcome - Pain intensity:* We assess participants’ average pain intensity over the past week via survey, at the four outcome assessment points using the Numeric Rating Scale of pain intensity (NRS-I) [25] an 11-point numeric rating scale (0 = no pain, 10 = worst pain imaginable). The primary outcome is the average weekly pain intensity at post-treatment.

*Secondary Outcomes – Pain intensity* will also be assessed daily during the trial via the IVR system using the NRS scale. Subjects will have a maximum of 77 daily scores: 7 daily calls for the baseline assessment week and 7 daily calls for each of the 10 weeks of treatment. We will use these scores to compute weekly means for each subject. The mean of seven daily assessments has been found to provide reliability in excess of 0.90 [26].

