IVR-based treatment methods facilitate the collection of daily patient-reported outcomes, which enable the examination of treatment processes. Little is known about the process by which people change their behavior and obtain treatment benefits, and commonly used analytic methods do not allow the fine grained depiction of the process of change between pre- and post-treatment, though there have been some investigations [37, 38]. Most existing models assume that the rate of change is constant over time, but outcomes and predictors may change over the course of treatment. In this study the collection of daily data over the course of 11 weeks provides high-frequency longitudinal data. These longitudinal data are appropriate for analytic methods like time varying effect models that allow us to examine change over time in both outcomes and predictors. These multiple assessment points enhance our ability to detect the shape of the curve associated with change and when in the treatment process change takes place (is it constant or does change occur primarily at a specific time during treatment). Thus variables that are thought to affect pain intensity like activity level, sleep, catastrophizing and skill practice are not assumed to be constant over the course of treatment, but are allowed to vary over time. This will allow us to determine the change over time in a number of factors thought to have an impact on pain intensity and compare the process of change in treatment responders (those who obtain at least a 30 % reduction in pain intensity at post-treatment) and non-responders.

CLBP is one of the most prevalent and costly healthcare problems in industrialized nations and a common reason for healthcare use [1, 39]. Given the large number of individuals who could potentially benefit from empirically validated treatments such as CBT for chronic pain, it is important that barriers to this treatment are addressed. An IVR-based CBT approach can be used to enhance care for patients when face to face access is not feasible.

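### Daily catastrophizing (and, less importantly, sleep quality) is first asked on treatment day 1, so the exploratory process-of-change analysis has no pre-treatment level for it

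*Protocol article*

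**What the plan says.** The Daily IVR calls section of the protocol article describes two call scripts. In the week before treatment, "participants receive seven daily IVR calls to assess their baseline pain intensity, pedometer-measured step counts and self-reported sleep duration in hours". The longer script begins later: "Starting on the first day of treatment and continuing for 70 days", participants answer "seven daily questions that assess pain intensity, sleep quality and duration, pedometer-measured step count, catastrophizing" and adherence to that week's skill goal. Two statements are given as the catastrophizing questions, one about worry that the pain will not end and one about not being able to stand it.

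The Outcomes section speaks of timing in general terms: "IVR outcomes will be assessed daily during the baseline week and over the 10 treatment weeks". For daily pain it gives the count as "7 daily calls for the baseline assessment week and 7 daily calls for each of the 10 weeks of treatment", a maximum of 77 scores.

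The Discussion builds a process analysis on these data: "In this study the collection of daily data over the course of 11 weeks provides high-frequency longitudinal data". It adds that "variables that are thought to affect pain intensity like activity level, sleep, catastrophizing and skill practice are not assumed to be constant". It says the data will be used to "determine the change over time in a number of factors thought to have an impact on pain intensity" and to compare the process of change in responders (at least a 30 % fall in pain intensity at post-treatment) with that in non-responders.

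**The concern.** The Discussion presents the daily series as a way to see the shape and timing of change between pre- and post-treatment. For a factor first measured once treatment has begun, the start of that curve is missing. The calls are made in the evening and cover the preceding 24 hours, so the earliest catastrophizing value is taken on the evening of treatment day 1. By Table 1, week 1 already introduces the rationale and the pain cycle, and week 2 takes up beliefs about pain.

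If a participant reports low catastrophizing in the first days, the data cannot show whether that person started low or improved early. That distinction matters for comparing the process of change in responders and non-responders. Pain, step count and sleep duration do have a pre-treatment week, so the variables in the same exploratory models would not share the same time span.

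**Working it through.** **Step 1: reproduce the plan's count.** Baseline calls 7, treatment calls 7 × 10 = 70. Total 7 + 70 = 77 calls, and 77 / 7 = 11 weeks. The 77 in Outcomes and the 11 weeks in the Discussion agree.

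**Step 2: count the items in each script (Daily IVR calls).**
- Treatment script: pain 1 + sleep quality 1 + sleep duration 1 + steps 1 + catastrophizing 2 + skill adherence 1 = 7. This matches the stated seven questions.
- Baseline script: pain 1 + steps 1 + sleep duration 1 = 3.

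**Step 3: coverage per item, as written.**

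| Item | Pre-treatment days | Treatment days | Maximum values | Weeks |
|---|---|---|---|---|
| Pain, steps, sleep duration (3 items) | 7 | 70 | 77 | 11 |
| Catastrophizing (2 items) | 0 | 70 | 70 | 10 |
| Sleep quality (1 item) | 0 | 70 | 70 | 10 |
| Skill adherence (1 item) | 0 | 70 | 70 | 10 |

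Three of the seven questions cover all 11 weeks and four cover 10. Skill adherence cannot have a baseline because no skill has yet been assigned. That leaves 4 − 1 = 3 items with an avoidable gap.

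**Step 4: look for another pre-treatment source.** The survey measures listed under Outcomes are the pain NRS, WHYMPI Interference, Roland-Morris, POMS, BDI-II and Veterans SF-36. The Baseline appointment section adds a brief interview on demographics and pain, the MINI and the SLUMS. None is presented as a measure of catastrophizing or of sleep quality.

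**Step 5: what the Discussion needs.** It names activity level, sleep, catastrophizing and skill practice. Activity (steps) has a baseline. Sleep has one through duration. Skill practice cannot have one. Catastrophizing is the one named factor that could have a baseline and does not.

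**Step 6: effect of the fix.** With the three items added to the baseline calls, each has 7 + 70 = 77 possible values, and 6 of 7 questions cover 11 weeks. The sample size does not enter this calculation and does not change.

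**The case against.** The strongest reply is that nothing confirmatory depends on these items. Catastrophizing and sleep quality are not outcomes at any tier, nor are they listed among the mediators in Aim 3 or the moderators in Aim 4. The Analysis section confines itself to primary and secondary outcomes, and the process models appear only in the Discussion. Time-varying effect models can be fitted to 70 daily values, and the modules aimed at negative thoughts come in weeks 6 and 7, after about five weeks of readings. All of this stands, and it limits the point to an exploratory analysis.

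Several stronger readings are tempting but not supported:
- **That the sections flatly contradict each other.** The Outcomes sentence on IVR timing need not cover items that are not outcomes. The 11 weeks in the Discussion are true of the calls and of three items, and its list includes skill practice, which cannot precede treatment. The wording is loose, and the Daily IVR calls section is the specific text.
- **That sleep has no baseline.** Sleep duration has one, and the Discussion says only sleep.
- **That an arm difference arising in week 1 is hidden.** Allocation is randomized, so such a difference remains visible as a direct contrast between arms. It would be lost only if week 1 were made the reference, which the article does not say.
- **That all change is unobservable.** Change from day 1 to day 70 is observed.

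A further fair objection is that the baseline week is not a clean reference. Randomization follows directly on the baseline assessments, the arm-specific handbook is handed out at the end of that appointment, and the seven calls come after enrollment. Participants may therefore have read treatment material before or during that week. This weakens the proposed reference but does not remove its value, since the week still precedes the first treatment day and serves the same role for pain, steps and sleep duration.

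The article may condense a fuller call script. But it states the content of both scripts itself, so the gap is not inferred from silence.

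**Conclusion.** The point holds in a limited form. As described, catastrophizing has at most 70 daily values and 0 of 7 pre-treatment readings, while the Discussion includes it in an analysis of change said to rest on 11 weeks. The same is true of sleep quality, with less consequence. The loss is the step from the pre-treatment level to the first treatment days, and the ability to separate a low starting level from an early response when responders and non-responders are compared.

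How large an early change might be cannot be judged from the document. The conclusion assumes that the article's item lists reflect the scripts actually used and that no undescribed measure supplies a baseline. The primary outcome, the secondary outcomes, the non-inferiority conclusion and the sample size are not touched. This is a cheap improvement to an exploratory analysis, not a flaw in the trial's main inference.

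**What to change.** Add the two catastrophizing items, and optionally the sleep-quality item, to the seven baseline calls. Use the baseline-week mean as the pre-treatment level in the exploratory process models, and note that this week follows randomization and handbook distribution. For participants already past that week, report these trajectories as on-treatment only. In the Outcomes and Discussion sections, state which IVR items cover 11 weeks and which cover 10.

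The cost is two or three existing prompts on calls that already take place, plus a short amendment. The downsides are slightly longer baseline calls and a missing baseline for participants already enrolled, whose pre-treatment values cannot be recovered.

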#### Skill practice and meaningful activity goals

Each week, participants are assigned a daily skill practice goal that corresponds to the specific pain coping skill presented in treatment that week (e.g., Week 4: practice deep breathing for 5 minutes each day). The *skill practice goal* for each week is described in the patient handbook for participants randomized to the IVR-CBT condition and is assigned by the therapist during the weekly treatment session for participants randomized to the in-person CBT condition. Participants in both conditions are assigned the same skill practice goals (see Table 1). As participants progress through treatment, they are encouraged to continue practicing skills learned in prior modules. Participants also create their own *goal for engaging in pleasant or meaningful activities* to promote behavioral activation (i.e., planned rewarding or productive activities in order to enhance mood and activity levels). Participants in the IVR-CBT condition are guided in this effort by information in the patient handbook. Participants in the in-person CBT condition collaborate in setting goals with their therapist during treatment sessions.

**Table 1 Tab1:** Treatment modules and goals for CBT and IVR-CBT

Week	Coping Skill	Description	Goals
0	None	Baseline assessment	None
1	Introduction	Present rationale for treatment, explain pain cycle and introduce goal setting.	- Complete one exercise each day in the “Your Guide to Setting Meaningful Activity Goals” section
2	Stretching	Introduce stretching, its benefits, explain acute vs. chronic pain, beliefs about pain and provide suggested stretches to practice.	-Practice stretches provided in the handbook daily
			-Set/ work on meaningful activity goal
3	Movement, Walking & Body Mechanics	Instructions for walking, body mechanics, increasing activity and preventing injuries.	-Practice body mechanics
			-Increase daily steps +10 % of prior week’s steps
			- Set/ work on Meaningful activity goal
			-Continue to practice prior week’s skill
4	Deep Breathing	Instructions for diaphragmatic breathing and its benefits.	-Practice diaphragmatic breathing using CD for 5–10 minutes/day
			-Increase daily steps +10 % of prior week’s steps
			- Set/ work on meaningful activity goal
			-Continue to practice prior weeks’ skills
5	Progressive Muscle Relaxation	Instructions for progressive muscle relaxation and its benefits.	-Practice progressive muscle relaxation using CD

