#### Weekly therapist feedback

Participants in the IVR-CBT condition receive a weekly, two to five minute pre-recorded personalized message from their therapist via the IVR system. On the last day of each week participants are told that they have a message from their therapist. This message may be accessed and replayed as often as the participants want. If participants miss the call that contains the feedback message, they are prompted to listen to the message during their next call. Participants and therapists may record messages to one another on the IVR system at any time during treatment. This allows participants and therapists to obtain clarification or feedback on specific topics and avoid frustration that may impair progress or prompt dropout.

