### Treatments

#### Overview

Both CBT conditions include 10 treatment modules delivered over 10 consecutive weeks. Treatments are delivered by either a PhD-level psychologist or the study nurse trained and supervised by a clinical psychologist with specific competencies and experience in delivering CBT for chronic pain. Therapists follow treatment manuals and participants are provided with a treatment-specific participant handbook. The 10-week course of therapy consists of an introductory module, followed by 8 consecutive pain coping skills modules, and concludes with a 10th module emphasizing skill consolidation and relapse prevention. Both conditions include the same pain coping skills, which were selected from a wider collection of possible skills because they were rated most highly by participants in a prior funded trial on importance, interest and ability to engage in them [21] (see Table 1 for description of skills). Participants assigned to both conditions continue to receive routine care of their CLBP by their current healthcare providers. Study staff do not attempt to influence clinical care other than CBT in any way.

*CBT* involves weekly, 30-minute, individual in-person sessions with a therapist, a pedometer-facilitated walking program and daily IVR assessment. Each session includes one treatment module.

Each module includes: (1) the presentation of an explicit rationale for development and use of the specific coping skill being taught, (2) a description of each coping skill, skill modeling and practice of the skill during the session, (3) problem-solving about the practice and use of the specific skill, and (4) assignment of a specific goal for practice of the week’s skill and collaboration between the therapist and participants to develop a weekly goal for engaging in pleasant or meaningful activities.

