#### Adverse events

Although walking is not considered risky for patients with chronic musculoskeletal pain and is often recommended, information about adverse events associated with participation in the walking portion of the treatment is solicited once per week during the IVR assessment calls. Participants may report adverse events by recording a brief audio message. These messages are reviewed each business day by study staff and any reports that indicate a cause for concern are followed-up with the participant, their primary care provider, or both.

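### The weekly adverse-event question covers only the walking programme, so harms from the assigned stretching and body-mechanics practice are left to spontaneous reports

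*Protocol article*

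**What the plan says.** Two sections of the protocol article define what is asked. Under Daily IVR calls, one of the once-weekly items is "any adverse events associated with the graduated walking portion of the treatment". Under Adverse events, "information about adverse events associated with participation in the walking portion of the treatment is solicited once per week during the IVR assessment calls". The scope is the same in both places, and participants in both arms receive the calls. The reason given there for asking concerns walking alone.

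Table 1 assigns other physical practice as well. The week 2 goal is "Practice stretches provided in the handbook daily". Week 3 adds "Practice body mechanics" alongside the first step goal. Weeks 3 to 10 each carry an instruction to keep practising what was taught earlier. The section on skill practice goals states that "Participants in both conditions are assigned the same skill practice goals".

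Delivery differs by arm. In-person modules include "a description of each coping skill, skill modeling and practice of the skill during the session" (Treatments, Overview). IVR-CBT participants learn the same skills from the handbook and optional recordings, and receive pre-recorded therapist feedback.

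Two open reporting routes are described: "Participants may report adverse events by recording a brief audio message" (Adverse events) and "Participants and therapists may record messages to one another on the IVR system at any time during treatment" (Weekly therapist feedback).

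**The concern.** A solicited adverse-event item is useful because everyone is asked the same thing at the same interval. Tying the item to one component of a multi-component programme limits that benefit to the one component. On the wording as paraphrased, a participant whose back worsens after stretching could truthfully answer that nothing happened in connection with walking. The item also asks the participant to judge cause before reporting.

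The participants have at least moderate chronic low back pain, some of it radicular or due to a specific spinal cause, and the week 3 module itself covers injury prevention. Injury during physical practice is therefore a subject that the programme already recognises. According to the Conceptual framework section, a finding of non-inferiority would lead to IVR-CBT being recommended to patients with chronic low back pain. Anyone weighing that recommendation will want harms data that cover the physical components, above all those taught with live modelling in one arm and from written and recorded material in the other. Follow-up of individual participants is also at stake, because staff act on what is reported to them.

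**Working it through.** The plan gives no figure on this point, so the check compares what is assigned with what is asked.

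**Physical practice assigned (Table 1, ten treatment weeks)**

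- Stretching: introduced in week 2 and carried forward by the weekly continuation goal through week 10. Weeks = 10 − 2 + 1 = 9.
- Body mechanics: introduced in week 3 and carried forward in the same way. Weeks = 10 − 3 + 1 = 8.
- Step goals (10 % above the prior week): weeks 3 to 10. Weeks = 10 − 3 + 1 = 8. The section on the walking programme confirms the week 3 start.
- In week 2, therefore, stretching is the only exercise assigned and the graduated walking goals have not begun. The article does not say whether the weekly walking item is asked before week 3.

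**What is asked or recorded about harm**

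| Component | Weekly solicited item | Other routes described |
|---|---|---|
| Walking | Yes, both arms | Audio message, message to therapist, mention at a session |
| Stretching | No | Same routes, volunteered |
| Body mechanics | Not named; taught in the same week 3 module as walking | Same routes, volunteered |

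The same weekly call asks whether participants still use skills from earlier weeks. It therefore records continued use of stretching but is not described as asking about harm from it.

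**What differs between arms**

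- The solicited item is the same in both arms, so the solicitation itself is not differential.
- Practice goals are the same, and daily home practice is unsupervised in both arms.
- The difference is the weekly 30-minute live session in the in-person arm, where the skill is modelled and practised and problems with its use are discussed. A session is also an occasion to mention a harm. No section says that therapists ask about harms.
- Open messaging is described under a heading that otherwise concerns the IVR-CBT arm, so it may offset part of that difference.

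**What is analysed**

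None of the four aims and none of the listed outcomes is a comparison of adverse events, and the Analysis section says that it covers primary and secondary outcomes only.

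**The case against.** The strongest reply is that the text describes one automated item, not the trial's whole adverse-event procedure. A journal article commonly leaves general and serious-event reporting to the full protocol. That stands, so the point is not that other procedures are absent. It is confined to the scope of the solicited item, which the article states in two places as walking.

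A second reply is that harms from stretching can still be reported. The sentence on audio messages is not limited to walking, messages are reviewed each business day, and the therapist can be messaged. A flare would also show in the daily pain rating or the weekly medication question, and in the IVR-CBT arm the therapist reviews the daily reports each week. This stands too: such harms are not invisible. But a volunteered report is not a solicited one, and a pain score identifies neither an injury nor the activity that led to it.

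Third, body mechanics is weak support, because it shares a module with walking and some participants would answer for both. That is accepted; stretching is the clear gap.

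A reader might go further and infer that the arms' safety comparison is invalid, or that IVR-CBT will look safer than it is. The document does not support either reading. It plans no such comparison, asks both arms the same question, and leaves home practice unsupervised in both. The direction of any reporting difference can only be guessed from unequal live contact.

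**Conclusion.** The point holds in limited form. The solicited harms data are incomplete because the weekly item is fixed to walking while both arms are also assigned stretching in 9 of the 10 treatment weeks and body mechanics in 8. Harms from these components, most clearly stretching, depend on spontaneous reports, for which the arms have unequal live therapist contact. Differential under-reporting is possible but not shown.

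The week counts measure how long the practice is assigned. They say nothing about how many events would be missed, and the article gives no event rate from which to estimate that.

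The conclusion rests on two assumptions: that the prompt as recorded matches the article's paraphrase, and that the continuation goal in Table 1 includes stretching through week 10. The primary non-inferiority analysis and the sample size are unaffected. The change is worth making because it improves ascertainment at little cost.

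**What to change.** Reword the weekly item, in both arms and in both sections that describe it, to ask about any new or worsened symptom or injury during any part of the programme. Add a keypad follow-up for the activity involved: stretching, walking, body mechanics, other or none. Report these solicited events by arm, separately from events volunteered by message or learned in therapist sessions, so that the by-arm table rests on a source that is the same in both arms.

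The article describes recruitment as under way, so record the date of the change and tabulate reports before and after it separately.

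The cost is re-recording one prompt, adding one follow-up question and making a short amendment. There are two downsides: more non-serious reports in the business-day review that staff already carry out, and an item definition that differs between early and late participants.
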